### Study design and setting

This study is a cluster randomised controlled trial implemented and reported in accordance with the requirements of the CONSORT statement [13] and its extension to cluster randomised trials [14]. The participants were randomly designated to either an intervention arm, which implements the usual care system and the peer support intervention, or a control arm which implements a usual care system, with geographical location being the unit of cluster randomisation.

All participants are patients with type 2 diabetes who receive primary health care at 12 rural community health centres located in Liu-he District, Nanjing, and Gao-gou Town, Huaian, in Jiang Su province. The study team coordinates and works hand-in-hand with the staff members at each community health centres to implement and monitor the study.

Figure 1 is a CONSORT diagram of the study design.

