#### Group allocation

Community health centres will be stratified by size and existing structure of primary diabetes care service. Allocation to intervention or control group is governed by a random number generation process using SAS 9.1 statistical software independently.

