### Outcome measures

Outcomes variables are measured at baseline, 6 months, and 12 months, to both participants and peer leaders. The primary expected outcome is the change in HbA1c at baseline compared to the sixth month and baseline to the twelfth month. HbA1c, a measurement of glycosylated haemoglobin, is regarded as the gold standard measure of glycemic control reflecting overall blood glucose values over the previous 8–12 weeks [30, 31]. There is a strong relationship between HbA1c and the risk of developing long-term diabetic complications and it is accepted as a reasonable surrogate for long-term outcomes in individuals with diabetes. Secondary outcomes are advanced glycation end products (AGEs) [32, 33], blood pressure, BMI, blood lipids, blood glucose (fasting plasma glucose and 2 hour post load glucose), patient-reported rates of severe hypoglycaemia, diabetes self-care activities, medication adherence, knowledge, quality of life, diabetes self-efficacy, traits, life satisfaction, depression, anxiety, and stress. In addition, cost is also assessed.

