### Data analysis

Social demographic data and health status of the study subjects are presented as frequencies (percentage) for categorical variables, and means ± standard deviations for continuous variables. Comparison of patients characteristics between groups will be checked by means of T-tests or χ^2^ tests, or non-parametric equivalents. Repeated measures analysis of variance and multilevel analysis for longitudinal data will be used to examine longitudinal differences between groups on primary and secondary outcome measures. Evaluation of intervention effectiveness will be by intention to treat using the above statistical tests. Evidence of clustering by clinic site and primary care provider will be examined and adjusted for analyses as needed. If significant differences in baseline characteristics are found, analyses will be repeated adjusting for these differences using ANOVA and logistic regression for multivariate analyses. Analysis of covariance (i.e. linear regression models for 12-month measurements with baseline scores and intervention arm as covariates) will estimate the changes from baseline to 12 months that can be attributed to the peer support intervention. Sensitivity analyses will be performed to estimate the effects of missing data using different assumptions (e.g. imputed values).The EuroQoL 5 dimensional health state measure (EQ5D) score at base-line and follow-up can be converted into utility weights using the EQ5D algorithm [34], which then allow for the calculation of quality adjusted life years(QALYs). Economic analyses will be employed to estimate direct and indirect cost analysis, the cost per QALY gained and incremental cost-effectiveness ratios. Sensitivity analysis will be undertaken to test the stability of the analysis in terms of the cost inputs and health outcomes. All analyses will be carried out with SPSS 10.0 software.

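### A significance-triggered rerun picks covariates from baseline tests that ignore clustering, with no rule on which result prevails, and the stated ANCOVA leaves out the stratification factors

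*Protocol article*

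**What the plan says.** Four statements in the protocol article bear on this point.

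- **Baseline testing** (Data analysis): "Comparison of patients characteristics between groups will be checked by means of T-tests", with chi-square and non-parametric tests as alternatives.
- **Trigger** (Data analysis): "If significant differences in baseline characteristics are found, analyses will be repeated adjusting for these differences using ANOVA and logistic regression for multivariate analyses".
- **Fixed covariates** (Data analysis, the sentence after the trigger): the ANCOVA is defined as "linear regression models for 12-month measurements with baseline scores and intervention arm as covariates".
- **Stratification** (Group allocation): "Community health centres will be stratified by size and existing structure of primary diabetes care service".

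The design is clustered, "with geographical location being the unit of cluster randomisation", and covers "12 rural community health centres". Clustering enters the analysis conditionally: "Evidence of clustering by clinic site and primary care provider will be examined and adjusted for analyses as needed". That sentence does not mention the baseline comparisons. The primary outcome, change in HbA1c at 6 and 12 months, is continuous.

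**The concern.** The trigger is a positive rule, not a detail that a condensed article leaves to another document. It has three weaknesses.

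1. **It selects on the wrong property.** Under randomisation a baseline p-value mostly measures chance. A strong predictor of HbA1c with p = 0.06 stays out, and an irrelevant variable with p = 0.04 goes in.
2. **The tests do not match the design.** Ordinary t and chi-square tests treat patients as independent. When whole locations are allocated, chance differences between a few centres appear as differences between arms and are called significant too often.
3. **Precedence is not stated.** The section already names repeated-measures ANOVA, multilevel analysis and ANCOVA. The rerun adds a result whose covariates are known only after the data are seen, and nothing says which result is the trial's answer.

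A related weakness is that centres are stratified by size and care structure, yet no model in the section names either factor. The ANCOVA, whose covariates are spelled out, holds only baseline score and arm. If the strata explain differences between centres, the precision gained by stratifying is not recovered in the analysis.

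**Working it through.** The article gives no figure for this rule, so there is none to reproduce. The check asks how often the trigger fires by chance, and what omitting the strata does.

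**Inputs from the article.** 180 patients per arm (Sample size calculation), so 360 in total; 12 centres (Study design and setting); 360/12 = 30 per centre.

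**Assumptions.** The centre is the cluster, centres are of equal size, and six go to each arm. The ICC is not given, so 0.01 to 0.05 is shown. Each test is at 5%, and baseline variables are independent of each other.

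**Step 1: false-positive rate of one baseline test that ignores clustering.** The design effect is DE = 1 + (30 − 1) × ICC, and the rate is 2 × [1 − Φ(1.96/√DE)].

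| ICC | DE | 1.96/√DE | Rate | Simulated (20,000 runs) |
|---|---|---|---|---|
| 0 | 1.00 | 1.96 | 5.0% | 4.9% |
| 0.01 | 1.29 | 1.73 | 8.4% | 8.4% |
| 0.02 | 1.58 | 1.56 | 11.9% | 12.0% |
| 0.05 | 2.45 | 1.25 | 21.1% | 21.4% |

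**Step 2: chance that at least one of k variables fires the trigger.** This is 1 − (1 − rate)^k. Table 1 lists 18 baseline-only items (10 demographic, 8 health status). Two of them, time of diagnosis and length of diagnosis, overlap, so k = 10 is shown as a cautious alternative.

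| ICC | k = 10 | k = 18 |
|---|---|---|
| 0 | 1 − 0.95^10 = 40% | 1 − 0.95^18 = 60% |
| 0.01 | 59% | 80% |
| 0.02 | 72% | 90% |
| 0.05 | 91% | 99% |

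With no clustering at all, 18 × 0.05 = 0.9 false triggers are expected.

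**Step 3: omitting the strata.** Centre-level outcomes were simulated (100,000 runs) for 12 centres in two balanced strata, three centres per arm in each, with no treatment effect. The share of between-centre variance explained by the strata is assumed.

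| Share explained | Type I error, strata ignored | Type I error, strata in model |
|---|---|---|
| 25% | 2.3% | 5.0% |
| 50% | 0.5% | 5.0% |
| 75% | under 0.1% | 5.0% |

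The test that ignores the strata rejects too rarely, because variation that stratification has balanced between arms is still counted as error.

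**The case against.** The strongest reply is that the main models do not depend on the baseline tests. The trigger governs a repeat, and the ANCOVA already holds the baseline score, normally the best predictor of follow-up HbA1c. This stands. A reader might infer that all adjustment is data-driven, or that prognostic information goes unused, and the ANCOVA sentence contradicts both. What remains is that the covariates of the rerun are picked by p-value and that its standing against the planned models is left open.

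A reader might also infer that logistic regression is meant for HbA1c. The text does not say so. It names ANOVA and logistic regression together, in a section covering primary and secondary outcomes, and some secondary outcomes, such as severe hypoglycaemia or medication adherence, could be analysed as binary. The wording is loose and deserves one clarifying clause, but it is not a demonstrated mismatch.

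On the strata, it is fair to say that a full covariate list often sits in an analysis plan, and one not shown here could add the two factors. This is the weaker half of the point. It survives because the article does spell out the ANCOVA covariates and the strata are not among them.

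Finally, the Step 2 percentages are illustrative. Correlated baseline variables would generally lower them, as would stratified allocation for variables related to the strata. They show how often the rerun would be triggered. They are not a type I error rate or a bias for the treatment effect, and should not be read as one.

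**Conclusion.** The point holds in a limited form and should be corrected. The trigger chooses covariates by chance imbalance, using tests that over-reject in this design: about 8%, 12% and 21% per variable at assumed ICCs of 0.01, 0.02 and 0.05 with 30 patients per centre. Even without clustering, at least one false trigger has a 40% chance with 10 independent variables and 60% with 18. A competing adjusted result is therefore likely, and the article gives no order of precedence.

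Leaving out the stratification factors costs precision and makes the test conservative. It might be taken to create false positives, but the simulation shows the opposite. That result assumes an analysis that accounts for centre and strata that explain part of the between-centre variance remaining in the model. Its size depends on the assumed share (25% to 75%).

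Neither part shows that the main treatment estimate is biased.

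**What to change.** 1. Delete the sentence that makes adjustment depend on significant baseline differences, and present baseline characteristics by arm descriptively, without tests.
2. Name one primary cluster-adjusted linear model for HbA1c, containing baseline HbA1c, arm, centre size and existing care structure, with each stratification factor coded in few levels.
3. List any further prognostic covariates in advance and label that analysis supportive, so that the primary model prevails.
4. State that logistic models, with cluster adjustment, apply to binary outcomes only.

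This is a change of wording that needs no new patients. Centre size and care structure must already be known for the allocation. The statistical cost is at least two centre-level degrees of freedom: 12 centres less two arms leaves 10, and two two-level factors reduce this to 8. Crossing the factors, or using more levels, costs more. The article does not give the number of levels, so the coding should be settled with that cost in view.

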### Sample size calculation

Sample size and power calculations are performed for the main outcome of interest-difference in mean HbA1c levels-using effect sizes and standard deviations derived from multiple published trials of patient-education interventions. Using a non-inferiority design based on clinically relevant difference of HbA1c of 0.5%, standard deviation of 1.5, and groups of 8–15 participants per randomisation group for 80% power at two-sided 5% significance, 150 participants are required to complete the study procedures. Allowing for a 20% drop-out from randomisation to completion of the trial, it is anticipated that we would require 180 subjects in each arm to be randomised in the study.

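### HbA1c change to 6 and to 12 months is primary, but a baseline-adjusted model is stated only for month 12; it should cover both visits

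*Protocol article*

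**What the plan says.** The Outcome measures section gives the primary outcome two time points: "The primary expected outcome is the change in HbA1c at baseline compared to the sixth month and baseline to the twelfth month". It also states the measurement times: "Outcomes variables are measured at baseline, 6 months, and 12 months, to both participants and peer leaders". Table 1 confirms that HbA1c is collected at all three visits.

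The Data analysis section then names three things that bear on HbA1c.

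- A longitudinal analysis that covers both follow-up visits: "Repeated measures analysis of variance and multilevel analysis for longitudinal data will be used to examine longitudinal differences between groups on primary and secondary outcome". No baseline covariate is named for it.
- A baseline-adjusted model: "Analysis of covariance (i.e. linear regression models for 12-month measurements with baseline scores and intervention arm as covariates". Its stated purpose is also limited to month 12; it "will estimate the changes from baseline to 12 months that can be attributed to the peer support intervention".
- A conditional re-analysis: "If significant differences in baseline characteristics are found, analyses will be repeated adjusting for these differences". This is not restricted to either visit.

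**The concern.** Two time points have equal standing as primary, but the model known to use baseline HbA1c efficiently is written for only one of them. The data do not require the difference, because baseline HbA1c is collected for every patient and serves month 6 as well as month 12.

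In ordinary repeated measures ANOVA, baseline is one of the repeated responses. The treatment effect at month 6 is then the arm-by-time contrast, that is, the difference between arms in raw change. That estimator is less precise than ANCOVA for any baseline-to-follow-up correlation below 1. It also responds to a chance baseline difference between arms through regression to the mean. The 6-month result could be weaker than the data allow, and could differ from the 12-month ANCOVA result partly because of the method.

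**Working it through.** **Inputs from the protocol (Sample size calculation).** A "clinically relevant difference of HbA1c of 0.5" percentage points, SD 1.5, two-sided 5%, 80% power, 150 completers (read as per arm, because the 180 to be randomised is per arm).

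**Assumptions.** The baseline-to-6-month correlation rho is not given, so a range of 0.3 to 0.8 is shown. SD 1.5 is read as the SD of the HbA1c level; the protocol does not say whether it is of level or of change. Clustering is ignored in the power figures.

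**The plan's own figure.** n per arm = 2 × (1.96 + 0.842)² × 1.5² / 0.5² = 141.3, so 142, against the stated 150. At 150 per arm the standard error is 1.5 × √(2/150) = 0.173 and power is Φ(0.5/0.173 − 1.96) = 82%. The gap between 142 and 150 does not affect this point.

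**Variance per patient, with σ = 1.5**

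- Unadjusted change: 2(1 − rho)σ²
- ANCOVA: (1 − rho²)σ²
- Ratio: 2(1 − rho) / [(1 − rho)(1 + rho)] = 2/(1 + rho)

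The standard error is √(2V/150), where V is the variance per patient, and power is Φ(0.5/SE − 1.96).

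| rho | SE, change | SE, ANCOVA | variance ratio | power, change | power, ANCOVA |
|---|---|---|---|---|---|
| 0.3 | 0.205 | 0.165 | 1.54 | 68% | 86% |
| 0.4 | 0.190 | 0.159 | 1.43 | 75% | 88% |
| 0.5 | 0.173 | 0.150 | 1.33 | 82% | 92% |
| 0.6 | 0.155 | 0.139 | 1.25 | 90% | 95% |
| 0.7 | 0.134 | 0.124 | 1.18 | 96% | 98% |
| 0.8 | 0.110 | 0.104 | 1.11 | 99.5% | 99.8% |

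If 1.5 is instead the SD of the change, the variance ratio is the same. Change-score power is then 82% at every rho, against 95%, 92% and 88% for ANCOVA at rho 0.3, 0.5 and 0.7.

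**Residual from a chance baseline difference d.** The change score shifts by −(1 − rho)d. For d = 0.2 this is −0.14 at rho 0.3, −0.10 at rho 0.5 and −0.06 at rho 0.7. A simulation of 10,000 trials at rho 0.5 agrees: the slope of the estimate on d is −0.50 for change and −0.01 for ANCOVA, with standard errors of 0.171 and 0.147.

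**These are two views of largely one loss.** 2(1 − rho) − (1 − rho²) = (1 − rho)², which is the variance that the (1 − rho)d term contributes. At rho 0.5 this is 1.00 − 0.75 = 0.25. The two effects must not be added together.

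**Does the conditional re-analysis protect month 6?** With 180 per arm and no clustering, the standard error of the baseline difference is √(2 × 2.25/180) = 0.158. A 5% test is triggered only above 1.96 × 0.158 = 0.31. A difference of 0.2 gives z = 0.2/0.158 = 1.26, p about 0.21, and passes unadjusted. At rho 0.5 it shifts the change estimate by 0.10, which is 0.10/0.5 = 20% of the target difference.

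**The case against.** The strongest reply is that the protocol does not specify an unadjusted change score at month 6. It names a multilevel longitudinal analysis without fixing how baseline enters. If baseline is a covariate, or a response with the arm means constrained equal at baseline, the analysis has about ANCOVA precision and leaves no such residual. A condensed article may leave that detail to the analysis plan. This stands, and it makes the loss conditional. It does not remove the point, because the article does fix the baseline-adjusted model explicitly and fixes it for month 12 alone. Repeated measures ANOVA, which is named first, does not impose equal baseline means.

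Three stronger readings are tempting, and the document does not support them.

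- A reader might infer that the 6-month effect keeps the whole baseline imbalance. It does not. A change score subtracts baseline and leaves only −(1 − rho)d, in the opposite direction. Over repeated randomisations it is unbiased; the shift is conditional on the observed d.
- A reader might infer that the two primary results come from two different methods. The longitudinal analyses cover both visits, and ANCOVA is an additional 12-month estimate.
- A reader might infer that imbalance goes unaddressed. Centres are to be stratified by size and existing diabetes care, and the conditional re-analysis could include HbA1c. The stratification does not use HbA1c directly, and a significance trigger is a weak safeguard, as the working shows.

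The size can also be small. Under the level reading of the SD, change-score power is at or above the planned 80% once rho is about 0.47 or more, and the gain is only 2 points at rho 0.7. The power figures ignore clustering, so they show the contrast between methods and not this trial's actual power. With clustered allocation, a baseline difference has a centre-level part that a patient-level slope need not remove in full.

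**Conclusion.** The point holds in limited form. Both visits are primary, and baseline adjustment is stated for one of them. Month 6 relies on analyses whose use of baseline is not stated, with a fallback that misses differences below about 0.3 HbA1c points. If baseline is treated as an ordinary repeated outcome, the 6-month variance is 33% higher than under ANCOVA at rho 0.5 and 18% higher at rho 0.7. This rests on a correlation the protocol does not give, SD 1.5 as the SD of the level, 150 completers per arm and no clustering. It is an improvement available at no cost and not a demonstrated failure of the trial: the text neither commits to the inefficient form nor rules it out.

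**What to change.** In Data analysis, extend the covariance model to both primary visits: linear models for HbA1c at 6 months and at 12 months, each with baseline HbA1c and arm as covariates.

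A single multilevel model would do the same and would also respect the design. The 6- and 12-month HbA1c values are the outcomes, baseline HbA1c is a covariate, an arm-by-visit term gives the effect at each visit, and a random effect represents the health centre. State that this adjustment applies whether or not any baseline test is significant.

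The cost is a change of wording and one degree of freedom for the baseline covariate. It needs no new data, patients or visits.

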### Qualitative evaluation

A descriptive parallel qualitative analysis is being carried out to record the attitude of patients, professionals, educators, rural clinicians and peer leaders to peer support and their experience of delivery in intervention practices. The peer leaders will voluntarily participate in a focus group, semi-structured interviews, or both, to assess how they experience the training and leading process. The focus group is designed to reveal the peer leaders’ general attitude and facilitate the development of the interview guide. Peer leaders are encouraged to discuss their feelings and efficacy, the training experience, motivations, as well as any positive and negative impacts on their own diabetes management. Semi-structured qualitative interviews and focus group with diabetic patients will also be carried out and analysed through the investigation and daily observations. The focus group and interviews are audio recorded and transcribed.

## Discussion

The World Health Organization’s action plan for chronic disease management helps encouraged governments to take action to aid people to better managing their own chronic conditions by providing education, incentives, self-management tools and care [35]. Implementation of a diabetes management plan should include clinical care, diabetes self-management education and ongoing support [36]. Self-management training and support is an effective component of care for people with diabetes. Due to a shortage of time and resources, this critical support is not consistently delivered in most health care settings. The study uses trained patients to provide peer support in urban community. We anticipate that patients in the intervention arm with a peer leader will show significant improvement in the biophysical and psychosocial outcomes, and so will the peer leaders. In addition, we hypothesize that the recruitment and training of volunteers with type 2 diabetes as peer leaders to support participants with the same conditions will be a cost-effective strategy. We expect that the qualitative and health economic research will reveal an in-depth perspective on the impact of this approach both at the level of the patient as an individual and at the societal level. Successful implementation of this trial will provide evidence of the key functions of peer support, identified by the global Peers for Progress program. Moreover, the results of this study will influence future policies on diabetes management, as well as other chronic diseases in China.
